### **1.9.2 Safety of Rabies vaccine**

Although associated with mild and transient reactions, all the cell-derived rabies vaccines are considered safe. With human diploid cell vaccines, which are most thoroughly investigated, pain, erythema and swelling or itching at the injection site occur among 30%–74% of the recipients. Systemic reactions involving headache, nausea, abdominal pain, muscle aches or dizziness are reported among 5%–40% of vaccinees, and allergic oedema in 0.1%. One study reports fever among 3.6% of recipients of the human diploid cell vaccine. Systemic allergic reactions characterized by generalized urticaria accompanied in some cases by arthralgia, angioedema, fever, nausea and vomiting have been reported. They are uncommon in persons receiving primary vaccination, but have occurred in up to 6% of persons receiving a booster dose, with onset after 2–21 days. These reactions have been shown to follow the development of IgE antibodies to  $\beta$ -propiolactone altered human serum albumin in the vaccine ( $\beta$ -propiolactone is used as an inactivating agent).

According to the manufacturers of purified Vero cell rabies vaccine and purified chick embryo cell vaccine, allergic reactions are very rare after both primary and booster doses with these vaccines. Studies of the purified vero-cell rabies vaccine reported local and general reactions in 10.6% of post-exposure treatment patients and complaints of mild to moderate reactions in 7%. Also, among intradermal or intramuscular recipients of this vaccine, low-grade fever was the only significant systemic event, occurring in 8% of all subjects and most frequently following intramuscular vaccination. In the same study, pruritus at the injection site was the only significant local reaction. Among 88 healthy adults receiving a total of 292 doses of purified chick embryo cell vaccine, 16.4% reported local side-effects, whereas 15.1% reported general symptoms.

In this study we shall use the recommended rabies vaccine in Gabon and all vaccinees will be closely monitored.

## **1.10 Potential Risks and Benefits**

### **1.10.1 Potential Risks**

Risks associated with both GMZ2 and rabies vaccine vaccinations include local inflammatory reactions to the injected product, such as injection site pain and swelling. Systemic effects generally associated with vaccines may include flu-like syndrome, fever, chills, nausea/GI symptoms, headache, malaise, myalgia and arthralgia. While rare, allergic reactions, including life-threatening anaphylaxis, are associated with many vaccine preparations and must therefore be considered as a potential risk in this study. Risks associated with drawing blood include fainting, infection and bruising.

Free medical treatment will be provided to enrolled participants during the active vaccination phase and the surveillance period, at a level that meets or exceeds the local Gabonese health care standards of medical diagnosis and treatment. Medical care for illnesses not related to

[figure not shown]

vaccination will not extend beyond the study period. Medical care for illnesses related to vaccination will extend, at minimum, until the condition has resolved or stabilized.

### **1.10.2 Known Potential Benefits**

Participants may not receive any direct benefit from the experimental vaccine in this study. However, they will receive follow-up medical care at the Albert Schweitzer Hospital. During the conduct of the study, participants randomized to receive rabies vaccine will benefit from this in the sense of the reduced risk of rabies, which is present in this region, where there is a large number of stray and domestic dogs which are not vaccinated. At the end of the study all participants will be informed of the vaccine they received. Participants randomized to the GMZ2 vaccine will be offered rabies immunization at that time. This will be done at the recommended schedule of 0, 7, 28 and 365 days.

Should this vaccine be successfully registered, the children in the Gabon and the entire sub-Saharan region endemic to malaria will benefit from the vaccine protection against malaria.

[figure not shown]

## 2 OBJECTIVES

### 2.1 Primary Objective

**To evaluate the safety and reactogenicity** of three doses of 30 and 100µg GMZ2, adsorbed on aluminium hydroxide, in comparison with three doses of the control vaccine (rabies), in healthy Gabonese children aged 1-5 years. This will be done through evaluation of the following:

1. Immediate reactogenicity; defined as any systemic adverse reactions occurring within 30 minutes after each injection,
2. Local and systemic reactogenicity measured from Day 0 to Day 14 after each dose,
3. Any unsolicited Adverse Event resulting in a visit to a physician between each injection and one month after the third dose,
4. Any Serious Adverse Event (SAE) occurring from the inclusion throughout the study.

Biological safety, one month after each vaccination, in reference with the baseline level the following :

1. RBC, haemoglobin, haematocrit, platelets and WBCs
2. Creatinine, ASAT, ALAT, total bilirubin and alkaline phosphatase.

### 2.2 Secondary Objectives

#### 2.2.1 Humoral Immune Response

**To assess the humoral response** to the vaccine antigens GMZ2, GLURP and MSP3 by measuring total IgG by ELISA. Anti-GMZ2 specific memory B-cell-responses and IgG-subtypes will be assessed by ELISPOT and ELISA, respectively.

1. IgG responses at Days 0, 28, 56, 84, and 365.
2. IgG subclasses at Days 0 and 84
3. Antigen-specific memory B-cells by ELISPOT at Days 0, 84, and 365

### 2.3 Exploratory Objectives

**To assess the functionality of the immune response** by measuring the Growth Inhibition of *P. falciparum* in the presence or absence of Monocytes, and by measuring the recognition of native antigen of *P. falciparum* by IFA.

[figure not shown]

### 3 STUDY DESIGN

This will be a randomised, controlled, double blind trial with three arms including: 10 children to receive 30µg GMZ2, 10 children to receive 100µg GMZ2 and 10 children to receive rabies vaccine.

#### 3.1 Overview

- Randomized, controlled, double-blind phase I study
- One trial centre
- Safety oversight by a Safety Committee
- Study monitoring by AMANET
- Screening will be done within 14 days prior to the first vaccination
- Vaccination schedule will be on study days 0, 28 +/- 3, and 56 +/- 3
- Route of administration will be intramuscular on the deltoid muscle, alternately starting with the left side.
- Study duration will be approximately 13 months per participant
- Each participant will attend 16 standardised visits at the trial centre (Inclusion visit D-14; D0; D1; D3; D7; D14; D28; D29; D31; D35; D42; D56; D57, D70, D84, D365).
- Blood samples will be taken by venopuncture at five time points at D-14; D0; D28; D56; D84, and D365. Biological parameters and serological will be assessed at these time points as well as serological parameters. A maximum total of 7.5 mL blood will be taken at each blood sampling. For each participant a maximum of about 37.5 mL blood will be taken during the whole study.
- Twenty four hours, 3 days, 7 days and 14 days after each vaccination a visit is planned to monitor adverse events at D1, D3, D7, D14, D29, D31, D35, D42, D56, D57, D 59, D63 and D70
- Follow-up of serious adverse events (SAEs) until resolution
- The primary analysis will be conducted for all primary and secondary endpoints at a data-lock-point one month post vaccination 3 (study Day 84), after which the Primary

[figure not shown]

Study Report will be produced. These results will be used to decide on the go criteria for the next trial in children.

- The study will then continue in a single-blind fashion. Data gathered during this period will be reported in an addendum report.
- At the end of the study participants will be informed which vaccine they received and those who received malaria vaccine will be offered immunization with the rabies vaccine.

### **3.2 Site description**

The study will be conducted at the Medical Research Unit of the Albert Schweitzer Hospital in Lambaréné Gabon. Lambaréné, a town with approximately 20,000 inhabitants, is located in the Moyen Ogooué province of Gabon near the equator in the Central African rain forest. There is very little variation in temperature and humidity throughout the year, but rainfall varies with considerably less rainfall during the dry season from July to August. A population of approximately 50,000 (Lambaréné and surroundings) inhabitants are served by two hospitals in Lambaréné, with approximately 90 % of children treated in the Albert Schweitzer Hospital.

The Medical Research Unit of the Albert Schweitzer Hospital was established in 1981 and is integrated in the routine services of the Albert Schweitzer Hospital. The scientific focus is on malaria research, and main areas of interest are parasite biology, pathophysiology, pathogen-host interaction, host immune response, clinical aspects and chemotherapy of malaria. Other areas of research include schistosomiasis, filariasis and mechanisms of allergy development.

The centre has an excellent track record of clinical trials, conducted to the standard of ICH - GCP guidelines and published in high-ranking journals. The centres track record of conducting malaria vaccine trials is increasing and presently the centre is involved with GMZ2 and GSK's RTS,S malaria vaccine trials.

### **3.3 Participant Inclusion Criteria**

- Children age 1-5 years inclusive at the time of screening;
- Residing in Lambaréné for the duration of the study;
- Written informed consent obtained before screening and study start, respectively;
- Available to participate in follow-up for the duration of study (13 months);
- General good health based on history and clinical examination.

[figure not shown]

### 3.4 Participant Exclusion Criteria

- Previous vaccination with any other malaria candidate vaccine.
- Concomitant vaccination with a investigational vaccine or a rabies vaccine;
- Use of a investigational or non-registered drug or vaccine other than the study vaccine(s) within 30 days preceding the first study vaccination, or planned use up to 30 days after the third vaccination;
- Chronic administration (defined as more than 14 days) of immuno-suppressants or other immune-modifying drugs within six months prior to the first vaccination. This includes any dose level of oral steroids or inhaled steroids, but not topical steroids;
- Confirmed or suspected immunosuppressive or immuno-deficient condition, including human immunodeficiency virus (HIV) infection;
- Confirmed or suspected autoimmune disease;
- History of allergic reactions or anaphylaxis to immunizations or to any of the vaccine components, or of serious allergic reactions to any substance, requiring hospitalization or emergent medical care;
- History of splenectomy;
- Laboratory evidence of liver disease (Alanine aminotransferase [ALT] greater than 1.25 times the upper limit of normal (<45 U/L) of the testing laboratory);
- Laboratory evidence of renal disease (serum creatinine greater than the upper limit of normal of the testing laboratory, or more than trace protein or blood on urine dipstick testing);
- Laboratory evidence of haematological disease (absolute leukocyte count  $5.4-14.8 \times 10^3/\mu\text{L}$ , absolute lymphocyte count  $2.34-7.11 \times 10^3/\mu\text{L}$ , platelet count  $192-646 \times 10^3/\mu\text{L}$ , or haemoglobin 8.5-12g/dL);
- Administration of immunoglobulins and/or any blood products within the three months preceding the first study vaccination or planned administration during the study period;
- Simultaneous participation in any other interventional clinical trial;
- Acute or chronic pulmonary, cardiovascular, hepatic, renal or neurological condition, malnutrition, or any other clinical findings that in the opinion of the clinical investigator, may increase the risk of participating in the study;
- Other condition that in the opinion of the clinical investigator would jeopardize the safety or rights of a participant in the trial or would render the participant unable to comply with the protocol.

[figure not shown]

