### 1.1.2 Malaria in Lambaréné (Gabon)

Malaria remains one of the leading public health problems in Gabon. The major vectors for malaria transmission are *Anopheles gambiae* and *A. moucheti* and the Entomological Inoculation Rate (EIR) in Lambaréné and its surroundings is about 50 infective bites per person per year (Sylla et al. 2000). There is little seasonal variability in transmission rates or parasite prevalence. *Plasmodium falciparum* is the predominant species and responsible for 95% of all infections. *P. falciparum* parasitaemia with clinical symptoms is infrequent in adults, and occur almost solely in school and pre-school children. The level of chloroquine resistance is high, nearly reaching 100 % both *in vitro* and *in vivo*. Recent data obtained from the Severe Malaria in African Children (SMAC) studies show that there is a fairly constant annual number of children admitted to the ward with *P. falciparum*, averaging about 500 children per year. On average, children aged 2-12 years experience about 1.5 malarial attacks per year, with a large variability among individuals. Anaemia is the most common complication, affecting about 70% of all malaria cases and, 17% of all hospitalised malaria cases have anaemia (Hb < 9 g/dL) or severe anaemia (Hb < 5 g/dL), respectively.

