## 5 PARTICIPANT PROCEDURES

### 5.1 Screening Day –14 to –1

The accepted process of reaching the community that has been established over the years between MRU and Lambaréné community will be followed. This requires that after the protocol is approved by the authorities, special information dissemination meetings are held starting with the key civic and traditional leaders. Awareness campaigns are then undertaken including peer communication groups before the reaching the stage of small groups of potential participants, and finally individuals.

After community information is disseminated as described, all interested guardians of potential participants will be invited to visit the study clinic on a specific date. They will receive oral and written explanation of the study, after which the screening consent will be obtained from those willing to participate. After the study has been explained to the parents/guardians of potential participants, they will be free to leave and return later with their decision; this will allow time for them to discuss the study with their family and carefully consider their involvement in the study.

All screening tests, medical history and examinations will be performed only after screening consent is obtained. Clinical Investigators will generally handle acute, simple conditions such as malaria or other acute infections. More complicated or chronic conditions, such as chronic renal or heart disease, will be referred to appropriate sources of medical care.

It is estimated that 50-60 children will be screened in order to obtain a list of at least 40 eligible participants. Participants will be recruited among children residing in Lambaréné.

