A screening form will be prepared for each participant and will later become part of the CRF for participants enrolled in the vaccine trial. A unique screening identification number will be assigned to each study participant. A medical history will be taken with special attention to recurrent infections to suggest immune suppression, previous history of splenectomy and prior vaccine reactions. Physical examination and laboratory screening tests will include: full blood count (FBC), creatinine, total bilirubin, ALT, AST, alkaline phosphatase. A participant who meets any of the exclusion criteria will be excluded. Participants excluded from this study because of significant abnormalities will be managed initially by Clinical Investigators and may be referred to the hospital for further evaluation as may be necessary. Screening tests will be completed within 14 days prior to entry into the study. Laboratory studies may be conducted at other times during the course of the trial if the investigators judge it necessary for the safety of the participant.

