### 8.3 Data Set to be analysed

#### 8.3.1 Definition of Population

Given the above mentioned considerations it is planned to enrol 30 participants in the trial, to be randomised into the three treatment arms.

The statistical analysis shall be performed on two types of population depending on the participant's compliance to the protocol:

**i). Per Protocol:** the vaccination, blood sampling and visits number as well as the time-interval between vaccination and follow-up visits are respected, as they are defined in the protocol and in the flow chart. All participants who have not been compliant with the protocol will be excluded from this analysis but will be described in the final report. The protocol compliance criteria are the following:

- Participants fulfilling the inclusion and exclusion criteria
- Participants who have respected the number of vaccination and the time-intervals between the vaccination:
  - V2: 1st vaccination: D0, interval V1+2 weeks (± 3days)
  - V7: 2nd vaccination D28 , interval V2+4 weeks (± 3 days)
  - V12: 3rd vaccination D56 , interval V5+4 weeks (± 3days)
  - V17: Post vaccination D84 , interval V12+4 weeks (± 7days)
  - V18: Last study visit D365 , interval V17+ 9months (± 14days)
  - Subjects having respected the number of blood samples for biological safety evaluation, as well as the intervals between blood samples on Days -14, 28, 56, 84 and 365 within their applicable intervals

[figure not shown]

**ii). Intention to treat:** All participants who have received at least one vaccine dose will be included in the analysis. However, if a participant is not vaccinated for reasons unrelated to the primary outcome measure and the participants' code was broken during the period of the study that participant will be excluded from further analyses. In the event a participant withdraws from the study due to side effects, the last observation will be carried forward in all subsequent analyses (Last Observation Carried Forward LOCF) of the primary outcome measure.

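### The haematology exclusion lists four ranges without saying whether values inside, below or above them exclude, and nothing else in the protocol settles which ends count

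*Protocol*

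**What the plan says.** Protocol section 3.4 lists laboratory evidence of haematological disease as a reason to exclude. The bullet begins "Laboratory evidence of haematological disease (absolute leukocyte count", gives ranges for leukocytes (5.4–14.8), lymphocytes (2.34–7.11) and platelets (192–646), all × 10³/µL, and ends "or haemoglobin 8.5-12g/dL". None of the four limbs carries a word or sign of direction.

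The two bullets before it do. Creatinine is excluded when "serum creatinine greater than the upper limit of normal of the testing laboratory". ALT is excluded when "greater than 1.25 times the upper limit of normal (<45 U/L) of the testing laboratory".

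Section 5.1 gives the operating rule: "A participant who meets any of the exclusion criteria will be excluded". It also gives the expected yield: "It is estimated that 50-60 children will be screened in order to obtain a list of at least 40 eligible participants".

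Section 5.3 and the visit entries for Days 0, 28 and 56 have the criteria reviewed before each vaccination. Section 8.3.1 makes "Participants fulfilling the inclusion and exclusion criteria" a condition of the per-protocol population.

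**The concern.** An exclusion criterion should name the finding that keeps a child out. This one names ranges that look like acceptable values. Taken as written, it points the wrong way.

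Supplying the missing word, outside, repairs only part of it. A two-sided range leaves open whether a high value excludes as well as a low one, and two careful screeners could decide differently on the same child.

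These are numerical entry limits for the first use of the product in children (section 1.8.3). Haemoglobin, platelets, white cells and ALT are also biological-safety measures judged against baseline (sections 2.1 and 7.1.1), so the entry rule helps to determine which baseline values are seen.

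**Working it through.** The check is mainly one of logic: apply the bullet under each reading and compare the result with the rest of the protocol.

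**Inputs.** The four ranges and the conjunction 'or' (section 3.4); any one criterion excludes (section 5.1). The blood counts below are illustrative only, in the order leukocytes, lymphocytes, platelets, haemoglobin.

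| Illustrative child | As written (inside a range excludes) | Outside either end excludes | Only below the lower end excludes |
|---|---|---|---|
| All mid-range: 10, 4.7, 419, 10.5 | excluded | not excluded | not excluded |
| All below: 3, 1.5, 100, 4.5 | not excluded | excluded | excluded |
| All above: 20, 9, 700, 13 | not excluded | excluded | not excluded |
| Only haemoglobin low: 10, 4.7, 419, 4.5 | excluded, by the other three limbs | excluded | excluded |
| Only haemoglobin high: 10, 4.7, 419, 13 | excluded, by the other three limbs | excluded | not excluded |

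**Step 1: the literal reading against the protocol.**
- Because of the 'or', one in-range value is enough to exclude.
- A haemoglobin of 4.5 g/dL does not trigger the haemoglobin limb, whereas 10.5 g/dL does. Section 1.1.2 describes patients who "have anaemia (Hb < 9 g/dL) or severe anaemia (Hb < 5 g/dL"), so 4.5 g/dL falls in the protocol's own severe category.
- The bullet's heading speaks of disease, and section 5.1 provides care for children turned away because something important was abnormal. Both point the opposite way from the literal rule.
- The planned yield is 40/60 = 67% to 40/50 = 80%. A rule that excludes for any in-range count cannot be what that plan assumes.

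**Step 2: what remains once 'outside' is inferred.** The third and fifth rows separate the two remaining readings. A child whose only out-of-range value is high (haemoglobin above 12 g/dL, platelets above 646 × 10³/µL) is excluded under one and eligible under the other. No other section states these limits. The yield does not help, because it is the result of all criteria together and the protocol gives no distribution of these counts.

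**Step 3: ALT.** If 45 U/L is the laboratory's upper limit of normal, the cut-off is 1.25 × 45 = 56.25 U/L. If 45 U/L is itself the cut-off, the implied upper limit is 45/1.25 = 36 U/L, a figure found nowhere in the protocol. A child with ALT above 45 and up to 56.25 U/L is eligible under the first reading and excluded under the second.

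**The case against.** The strongest reply is that no experienced site would follow the literal rule. Section 3.3 requires general good health, the bullet is headed as evidence of disease, and the recruitment plan assumes that most screened children qualify. This stands. A reader might infer from the wording that no healthy child could enter the trial, but the protocol's own context makes that an unrealistic outcome.

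A reader might also want to put a pass rate on each reading. The documents do not support one. They do not say what share of healthy children each range covers, and the limbs are not independent, since lymphocytes are part of the leukocyte count.

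Nor is there a case for bias between arms. Allocation is randomised from the list of eligible children, the laboratory measures are referred to baseline, and section 8.6 calls the analysis descriptive. Section 8.4 bases the primary analysis on everyone who received at least one dose and mentions the per-protocol analysis for the secondary and exploratory outcomes.

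On ALT, the bracket sits directly after the reference to the upper limit, so reading 45 U/L as that limit is the more natural course. The item is loosely written, not inverted.

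What survives is that the stated rule lacks a direction where its neighbours have one, and that good sense cannot tell a screener whether the upper ends exclude. Loss of symbols in the text at hand is an unlikely explanation: the less-than sign in the ALT bullet is intact, and all four limbs lack a direction.

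**Conclusion.** The point holds as a drafting error in an operative eligibility rule. As written, the haematology bullet contradicts its own heading, section 5.1 and the planned screening yield. The intended sense, that abnormal values exclude, can be inferred. Whether one end or both ends exclude cannot.

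The effect is on who is enrolled and described, and on who counts as per-protocol. With 10 children per arm, one eligibility call that goes either way is 1/10 = 10% of an arm. How many children would be affected cannot be worked out from the protocol. The ALT wording is a minor ambiguity spanning 45 to 56.25 U/L.

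The conclusion rests on the text alone and needs no assumption about the distribution of blood counts. The bullet should be corrected before screening, but the error does not undermine the design.

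**What to change.** The sponsor should reconcile the bullet with its heading by restating each of the four limbs with an explicit direction. Its clinicians should confirm, limb by limb, whether the lower end, the upper end or both exclude. No limit is proposed here.

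The same wording should go on the screening form and be the one that the pre-vaccination reviews and the per-protocol definition in section 8.3.1 rely on. In the ALT bullet, say whether 45 U/L is the laboratory's upper limit of normal or the cut-off itself.

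The cost is two reworded bullets and matching edits to the screening form and section 8.3.1. No test, visit or participant is added.
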